## Abstract

**Background:**

Falls are a leading cause for emergency department (ED) visits in older adults. As a fall is associated with a high risk of functional decline and further falls and many falls do not receive medical attention, the ED is ideal to initiate secondary prevention, an opportunity generally not taken. Data on trajectories to identify patients, who would profit the most form early intervention and to examine the impact of a fall event, are lacking. To tailor interventions to the individual’s needs and preferences, and to address the whole scope of fall risks, we developed this longitudinal study using an extensive assessment battery including dynamic balance and aerobic fitness, but also sensor-based data. Additionally, participative research will contribute valuable qualitative data, and machine learning will be used to identify trips, slips, and falls in sensor data during daily life.

**Methods:**

This is a mixed-methods study consisting of four parts: (1) an observational prospective study, (2) a randomized controlled trial (RCT) to explore whether a diagnostic to measure reactive dynamic balance influences fall risk, (3) machine learning approaches and (4) a qualitative study to explore patients’ and their caregivers’ views. We will target a sample size of 450 adults of 60 years and older, who presented to the ED of the Klinikum Oldenburg after a fall and are not hospitalized. The participants will be followed up over 24 months (within four weeks after the ED, after 6, 12 and 24 months). We will assess functional abilities, fall risk factors, participation, quality of life, falls incidence, and physical activity using validated instruments, including sensor-data. Additionally, two thirds of the patients will undergo intensive testing in the gait laboratory and 72 participants will partake in focus group interviews.

**Discussion:**

The results of the SeFallED study will be used to identify risk factors with high predictive value for functional outcome after a sentinel fall. This will help to (1) establish a protocol adapted to the situation in the ED to identify patients at risk and (2) to initiate an appropriate care pathway, which will be developed based on the results of this study.

**Trial registration:**

DRKS (Deutsches Register für klinische Studien, DRKS00025949). Prospectively registered on 4^th^ November, 2021.

**Supplementary Information:**

The online version contains supplementary material available at 10.1186/s12877-022-03261-7.

## Background

Falls are a main reason for emergency department (ED) visits in older adults [1]. Around 33% of community-dwelling older adults fall at least once a year with many of them becoming recurrent fallers [2, 3]. Falls diminish quality of life and increase mortality and morbidity [4]. As fall incidence and severity rise with age, falls will continue to be a burden for healthcare systems worldwide, especially in the context of the demographic change [3, 5].

Numerous risk factors for falls have been identified such as age, sex, cognitive decline, vertigo, muscle weakness, (dynamic) balance dysfunction, or polypharmacy [6–9]. Consequences of falls include physical as well as psychosocial sequelae. Physically, about 14% of falls lead to fractures, and around 10% of falls result in traumatic head injuries [10, 11]. Psychosocially, falls may cause fear of falling, which is a relevant fall risk factor itself, with prevalence ranging between 30 to 73% [12, 13]. Fear of falling may result in reduced physical activity [14], and affect social participation, thus, increasing the risk of social isolation and loss of independence [15, 16]. Therefore, the manifold consequences of falls do not only impair quality of life, but also increase the risk of further diseases and disorders such as depression and dementia [16–18], potentially forming a vicious circle.

Individuals presenting to the ED with a fall, who are directly discharged, are an easy to identify, but yet understudied high-risk group for further falls and functional decline [19, 20]. To optimize patient care, it is crucial to initiate secondary prevention programs for these individuals as they seek medical attention in the ED. Long term observation of this group may enable the identification of different functional trajectories [20, 21], thereby providing a solid basis for well-founded decision-making, and tailored falls prevention interventions in the future.

To identify functional trajectories, a comprehensive geriatric assessment is needed, whose informative value can be improved by modern sensor technology. Further, an in-depth analysis of fall risk factors is mandatory. As dynamic reactive balance and aerobic fitness are not only discussed to be relevant fall risk factors but may also present treatment targets for future trials, they should be included in such an assessment battery. Dynamic balance dysfunctions are known to increase fall risk [7–9]. However, previous research indicates that even a single perturbation-based dynamic balance session influences functional trajectories and fall risk positively [22]. Therefore, observational studies using perturbation to assess dynamic balance have to control for potentially confounding effects of such a diagnostic session. The role of aerobic fitness as a risk factor is less clear and its association with static balance mostly based on cross-sectional findings [23, 24], making it a promising research target for longitudinal studies.

The worrying sequelae of falls for the individual but also their societal impact, call for action to strengthen and establish effective prevention programs, promoting high compliance of the participants [25]. Here, it is essential to take the populations’ specific needs into account. Patient-centered approaches have gained importance to identify potential barriers and facilitators to ensure adherence to such programs [26]. Therefore, exploring patients’ and their caregivers’ views on falls prevention seems crucial to build a realistic foundation for tailored intervention programs [27, 28].

The SeFallED study aims to identify long-term trajectories of older adults, presenting to the ED without hospital admission, after a sentinel fall. The study will combine geriatric assessments, sensor data and machine learning approaches. Further, the prognostic value of different, so far rarely studied risk factors such as aerobic fitness and dynamic reactive balance in predicting the trajectories, while controlling for potentially confounding effects of the respective risk factor assessments will be analyzed. Finally, these results will be combined with information on individual barriers, preferences and needs from the patients’ and caregivers’ perspectives to select and evolve adequate fall prevention programs in the future.

## Methods/design

### Study design

This study protocol describes a mixed-methods study, consisting of four parts: (1) an observational prospective study to identify different trajectories of performance on activities of daily living, (2) a randomized controlled trial using a parallel group design (1:1) to explore whether a diagnostic to measure reactive dynamic balance influences fall risk, (3) machine learning a) to record data using inertial measurement units (IMU) and (depth-) cameras of human reactions to standardized perturbations in order to train classifiers and b) to identify slips, trips, and falls from IMU sensor data in real life, and (4) a qualitative study to explore patients’ and their caregivers’ views on falls prevention to identify facilitators and barriers for future interventions [29]. A patient advisory board consisting of older adults that have experienced fall(s) will accompany this study.

The study will be conducted at the Carl von Ossietzky University in Oldenburg, Germany from October 2021 until January 2024, in accordance with the Declaration of Helsinki and was approved by the Medical Ethics Committee of the University of Oldenburg (number 2021 – 120). All participants will provide written informed consent to participate in the study. The consent forms are designed to be signed by either the participant or if needed by the participant and his / her legal guardian or family member. Ethical guidelines for research conducted with adults that lack the capacity to give consent will be followed and include the principle of group, the subsidiarity principle and the minimal risk standard [30]. Further, study information has been adapted to facilitate the participant’s understanding of the study, which will be provided in addition to the regular consent form, if necessary. Figure 1 shows the study design in a flow diagram.

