### Participants and recruitment

It is the aim to recruit 450 older adults, who meet the following inclusion criteria: 1) age 60 years or above, 2) presented to the ED of the Klinikum Oldenburg after a fall and were discharged within 72 h, 3) informed consent.

Exclusion criteria are as follows: 1) life expectancy of less than 3 months, 2) unstable medical, neurological or psychiatric condition, 3) bedridden or being unable to walk without support of another person, 4) residence more than 20 km away from the research center, 5) acute psychosis or social aggression, 6) inability to communicate verbally in German or English. Furthermore, participants that 1) are completely dependent on walking aids 2) or subjectively not able to walk 400 m in less than 5 min will be included in the observational part of the study but deemed ineligible for visiting the gait laboratory.

A study nurse will be present at the ED from Monday to Friday during regular working hours and address all suitable individuals to obtain written consent for further contact. These individuals will be contacted within a week of their visit to the ED to schedule an appointment for the first home assessment during which written consent for participation will be provided. The staff in the ED will hand out flyers with relevant information for participation and contact data outside regular working hours of the study nurse. Recruitment will be ongoing between October 2021 and January 2023.

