### Data assessment

Data will be collected at the ED, in participants’ homes and at the gait laboratory. Furthermore, IMUs to measure physical activity as well as gait parameters will be worn by the participants during daily life over 7 days at each time point (T1 – T4). After the initial assessment, the researchers maintain contact with the participants through monthly phone calls, as part of the prospective falls recording in addition to fall calendars (Fig. 1). Within four weeks after presenting to the ED, participants will be visited at home for the first functional assessment (T1), which will be repeated after 6 (T2), 12 (T3) and 24 (T4) months. Besides the data collected during the home assessments, eligible participants will attend testing in the university’s gait laboratory. This appointment will preferably be scheduled a week after the respective home assessments.

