## Discussion

As falls are a major public health problem, the World Health Organization called for effective intervention strategies in their report ‘Step Safely’, published in 2021 [78]. The SeFallED study will aid in developing such strategies by systematically assessing the risk of older adults who presented to the ED after a fall, a group at high risk for further falls [79].

One strength of the SeFallED study is its long observation period (> 12 months), which may be increased by further funding, with yearly follow-up visits and monthly telephone calls. While fall research guidelines demand a prospective data collection for at least up to 12 months [80], it is likely that long-term consequences of a fall may either last well beyond this period or may only manifest after a certain time has passed [81]. Our long-term data will provide better insight and deepen our understanding of the consequences of falls in older adults, which is needed to design tailored interventions and to inform healthcare professionals and policy makers.

Another strength of the SeFallED study is its mixed methods approach, which combines both qualitative and quantitative data and includes machine learning aspects. Whereas quantitative data is needed to calculate risk scores that may facilitate decision making processes in the future, the qualitative approach, involving patients’ representatives, may enhance appropriateness and relevance of the research, and hence the quality of the study [26, 82]. Especially the collaboration with a PRT has shown promise to benefit the research process as well as its outcomes [83]. The potential of smart systems to enhance care for older adults, but also to detect falls or gait insecurities has been acknowledged in previous research [84, 85]. Therefore, adding machine learning to the observational data of older individuals after a sentinel fall, may offer a broad spectrum of innovative approaches in fall risk assessment, but also falls prevention.

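### The stated study dates cannot deliver the 24-month assessment (T4) scheduled for everyone; only people entering up to about January 2022 can reach it

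*Protocol article*

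**What the plan says.** The Study design section dates the conduct of the study "from October 2021 until January 2024". Participants and recruitment adds: "Recruitment will be ongoing between October 2021 and January 2023". The target there is stated as "It is the aim to recruit 450 older adults".

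The abstract's Methods paragraph says "The participants will be followed up over 24 months". Data assessment places the first home visit in the four weeks after the ED attendance and describes it as an assessment "which will be repeated after 6 (T2), 12 (T3) and 24 (T4) months". Table 1 lists T4 for every repeated instrument and for the fall calendar. None of these places limits T4 to part of the cohort.

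Two other sections read differently. Statistical analysis names T1, T2 and T3 and then refers only to later annual examinations, without naming T4. The Discussion gives the observation period as longer than 12 months, "which may be increased by further funding".

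**The concern.** The end of conduct falls 12 months after the end of recruitment. That fits a 12-month visit for the last entrant, not a 24-month one. Anyone who enters after about January 2022 cannot have T4 within the stated period, however well they adhere.

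At stake is how much information the second year of follow-up holds. Long-term trajectories are the declared aim, and the length of observation is claimed as a strength, yet second-year data would come from a minority who entered in one autumn and winter. The article gives no expected number at T4, so a reader would assume something close to 450 less dropout.

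**Working it through.** **Inputs from the protocol article**
- Conduct: October 2021 to January 2024 (Study design).
- Recruitment: October 2021 to January 2023 (Participants and recruitment).
- T1 at 0 to 4 weeks after the ED visit, T4 at 24 months (Data assessment).
- Target 450 (Participants and recruitment).
- 1,182 ED patients in 2018, 48% ineligible, a further 38% not consenting (Sample size).
- Registration on 4 November 2021, described as prospective (Trial registration).

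**Assumptions.** The article gives months, not days, and no accrual curve. Uniform accrual is assumed unless stated otherwise.

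**Step 1: latest entry that allows T4.** January 2024 minus 24 months is January 2022. If the 24 months run from T1 and T1 is four weeks after the ED visit, the limit is four weeks earlier. This step needs no accrual assumption.

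**Step 2: follow-up guaranteed to the last entrant.** January 2023 to January 2024 is 12 months. If T3 is counted from a late T1, even T3 can slip just past the end date. Across the date variants tried, T3 is reachable for about 87 to 100%.

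**Step 3: share able to reach T4.** Share = (latest entry allowing T4 − recruitment start) / (recruitment end − recruitment start).

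| Assumption | Share | Of 450 |
|---|---|---|
| Whole months, month to month | 3/15 = 20% | 90 |
| Whole months, inclusive | 4/16 = 25% | 113 |
| 1 Oct 2021 to 31 Jan 2023, counted from ED visit | 123/488 days = 25.2% | 113 |
| Same, counted from T1 at 28 days | 95/488 days = 19.5% | 88 |
| Start 4 Nov 2021, from ED visit | 89/454 days = 19.6% | 88 |
| Start 4 Nov 2021, from T1 at 28 days | 61/454 days = 13.4% | 60 |
| Start 4 Nov 2021, from T1 at 28 days, study end taken as 1 Jan 2024 | 30/453 days = 6.6% | 30 |

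The article's own recruitment figures imply faster accrual: 1,182 × 0.52 × 0.62 = 381 per year, or 31.8 per month. Four months then give 127, and 127/450 = 28%. The overall range is therefore about 7 to 28%, all before dropout.

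**Step 4: precision.** For a simple mean at T4, the standard error relative to a full cohort grows by √(450/113) = 2.0 to √(450/90) = 2.2. A mixed model recovers part of this from the earlier visits.

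**Step 5: the Friedman test.** Statistical analysis falls back on this test for whole-group trajectories when residuals are not normal. In its standard form it needs complete blocks. If T4 were one of the time points, 450 − 113 = 337 to 450 − 90 = 360 people (75 to 80%) would drop out of the test under uniform accrual.

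**The case against.** The strongest reply is that Statistical analysis and the Discussion already treat visits after 12 months as open-ended and partly dependent on funding. Together with an end date exactly 12 months after recruitment closes, this looks like a 12-month core study whose extension was loosely worded. That may well be the intention, but it does not remove the conflict, because the abstract, the visit schedule and Table 1 present T4 as planned for all.

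Several objections limit the consequences, and they stand:
- No endpoint, hypothesis or sample size is fixed at 24 months. The 450 comes from ED volume. A reader might infer that the study fails a stated 24-month conclusion for 450 people; the article states no such conclusion.
- A reader might infer that T4 results would be biased. Absence of T4 decided by entry date is administrative censoring, largely compatible with the planned likelihood analysis under missing at random, and late entrants still contribute T1 to T3. This protection is stated for parametric models only, so it does not extend to the Friedman test.
- A reader might infer serious seasonal confounding. T1, T3 and T4 fall in the same season for each person, so within-person change over 12 or 24 months is season-matched. What remains is that autumn and winter index falls may not represent the rest. Adjusting T4 results for season or calendar period would not help, because everyone with T4 would have entered within about four months.
- The 17% dropout is stated for the randomised subgroup, so applying it to the cohort's T4 counts is not supported.
- The randomised trial is not shown to be affected, because no time horizon is stated for its fall outcome.

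**Conclusion.** The point holds as an internal contradiction. The stated conduct and recruitment periods cannot give the whole cohort the 24-month follow-up that is scheduled without restriction; they secure about 12 months for the last entrants. That T4 is confined to entrants up to about January 2022 follows from the dates alone.

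The share is conditional: about 20 to 25%, roughly 90 to 113 of 450 before dropout, under uniform accrual from 1 October 2021, and about 7 to 28% when the start date, accrual rate, end date and T1 delay are varied. The main effect is a large loss of precision for second-year trajectories, which would rest on early, autumn and winter entrants. A Friedman test that included T4 would also lose most of the cohort.

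**What to change.** Reconcile the end of conduct, the recruitment period and the T4 schedule in one of two ways.

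1. If funded, state that conduct runs through the last T4. Entry in January 2023 plus 24 months is January 2025, or February 2025 with a four-week delay to T1. This is 12 to 13 months beyond the stated end.
2. Otherwise, state 12 months (T3) as the follow-up for all. Describe T4 as a funding-dependent extension and give its expected number under a stated accrual assumption. Align the abstract, Data assessment, Table 1, Statistical analysis and Discussion. Say whether visits are counted from the ED attendance or from T1, so that T3 for the last entrants fits the end date.

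Under the second option, record T4 values missing because of entry date as administrative, separately from dropout, and limit whole-cohort Friedman tests to T1 to T3.

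The first option costs funding for the remaining visits. The second is mainly rewording here and in the registration where it carries the same claim. Its drawback is a less favourable statement of the follow-up.

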**Fig. 1 Fig1:**
[figure not shown]
Flow diagram for the study design (FIT = participants with sufficient walking ability; FIT + AGP Aerobic fitness, Gait analysis and Perturbation based dynamic balance; FIT + AG = Aerobic fitness and Gait analysis)

### Participants and recruitment

It is the aim to recruit 450 older adults, who meet the following inclusion criteria: 1) age 60 years or above, 2) presented to the ED of the Klinikum Oldenburg after a fall and were discharged within 72 h, 3) informed consent.

Exclusion criteria are as follows: 1) life expectancy of less than 3 months, 2) unstable medical, neurological or psychiatric condition, 3) bedridden or being unable to walk without support of another person, 4) residence more than 20 km away from the research center, 5) acute psychosis or social aggression, 6) inability to communicate verbally in German or English. Furthermore, participants that 1) are completely dependent on walking aids 2) or subjectively not able to walk 400 m in less than 5 min will be included in the observational part of the study but deemed ineligible for visiting the gait laboratory.

A study nurse will be present at the ED from Monday to Friday during regular working hours and address all suitable individuals to obtain written consent for further contact. These individuals will be contacted within a week of their visit to the ED to schedule an appointment for the first home assessment during which written consent for participation will be provided. The staff in the ED will hand out flyers with relevant information for participation and contact data outside regular working hours of the study nurse. Recruitment will be ongoing between October 2021 and January 2023.

### Randomization and blinding

Two thirds of the 450 participants will take part in the tests in the gait laboratory. To control for the potential influence of assessing dynamic balance, these 300 participants will be randomly allocated to either a perturbation or no perturbation group using a 1:1 ratio block randomization. Randomization will be stratified in four different strata based on sex (male / female) and cognitive status (normal / impaired). We will stratify participants into cognitively normal and cognitively impaired using the result of the Montreal Cognitive Assessment (MoCA) at the first home visit. The chosen cutoff of ≤ 24 points increases sensitivity and specificity of the MoCA and reduces false positive results [31–33]. The randomization lists will be prepared by an independent statistician and will not be accessible by the persons enrolling the subjects into the study. The lists will be stored on a secured data server and protected by a password only known by the principal and co-investigators. Assessors of functional performance and falls risk factors will be blinded to allocation.

### Data assessment

Data will be collected at the ED, in participants’ homes and at the gait laboratory. Furthermore, IMUs to measure physical activity as well as gait parameters will be worn by the participants during daily life over 7 days at each time point (T1 – T4). After the initial assessment, the researchers maintain contact with the participants through monthly phone calls, as part of the prospective falls recording in addition to fall calendars (Fig. 1). Within four weeks after presenting to the ED, participants will be visited at home for the first functional assessment (T1), which will be repeated after 6 (T2), 12 (T3) and 24 (T4) months. Besides the data collected during the home assessments, eligible participants will attend testing in the university’s gait laboratory. This appointment will preferably be scheduled a week after the respective home assessments.

